Previous e-health studies on dementia caregivers show positive effects on caregiver confidence, stress, depression, and self-efficacy with effect sizes ranging from 0.2 to 0.3 [17]. Provision of tailored information, a coach, and the opportunity to interact with other caregivers shows the most promise [17]. Blending face-to-face guidance with online modules increases caregivers’ connection with the therapist and adherence [18, 19]. However, research on the effects of e-health on dementia caregivers lacks methodological rigor [17], and adverse effects of caregiving are often addressed in the later stages of dementia, when caregivers already feel overburdened [20]. Despite their low levels of life satisfaction and high levels of overload, caregivers do not use services in the early stages because they do not feel the need for such services or because they struggle with acceptance due their experience of stigma [20–22]. Supporting caregivers in the early stages of dementia could prevent high levels of burden and psychological problems in them in the later stages and delay institutionalization [23–26]. However, early-stage dementia caregiver support can be experienced adversely if the care does not suit the caregiver’s personal situation or the stage of the disease. Negative and stigmatizing information can make it difficult for caregivers to identify with and may hamper acceptance [20]. Learning to positively manage life with dementia, instead of managing the dementia itself in a self-management program, could facilitate caregivers’ adaptation to their new caregiving role. A focus on enhancing positive, intact experiences that are tailored to the individual caregiver’s situation may be more effective in increasing caregiver self-efficacy and reducing the negative consequences of caregiving at the later stages [20].

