### Study aim and hypotheses

The current paper presents the design of a randomized waiting-list controlled trial investigating the effects of the blended care self-management program “Partner in Balance.” Alongside the effectiveness study, a process evaluation will be conducted to evaluate internal and external validity. As recommended by the Medical Research Council (MRC) Framework for the design and evaluation of complex intervention [27], the program was based on existing literature [17], theory, and user and professional input [28]. In a pilot evaluation, caregivers reported increased feelings of self-efficacy and goal attainment post intervention. Feedback from the feasibility study was used to adapt the intervention to increase user-friendliness [28]. The next objective is to evaluate the process characteristics, effectiveness and cost-consequence of “Partner in Balance.” Specifically, we aim to investigate (1) the internal and external validity of the intervention based on sampling quality (recruitment, randomization and reach) and intervention quality (relevance, feasibility, and performance according to protocol) prior to the effect analysis to evaluate credibility and generalizability [29], (2) whether “Partner in Balance” is superior to the waiting-list control condition in terms of participants’ subjective well-being, as evidenced by improved subjective self-confidence (increased self-efficacy) and goal attainment and lower levels of psychological complaints (depression, anxiety and stress) following the self-management intervention, and (3) whether these effects are maintained after 3, 6 and 12 months, and lastly (4) the cost-consequence of “Partner in Balance” is calculated to estimate the impact of the intervention on resource use, costs, and health outcomes.

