### Sample size

We determined our sample size based on previous online intervention studies on caregivers of people with dementia using the CSES as outcome measure, the use of repeated measures, within-between interaction with a mean effect size of 0.2 [55], the following assumptions: alpha 0.05, power 85 % and 25 % loss to follow-up. In accordance with these criteria, we aim to enroll 80 participants (40 participants per group).

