To analyze changes in the primary and secondary outcomes during the total study period, the data from the intervention-only group and the waiting-list group receiving the intervention after 8 weeks will be combined using a linear mixed model (LMM). The LMM will estimate fixed effects (regression slopes) for the change during the waiting-list interval (T0–T1 as measured in the waiting-list group only) and fixed effects for change in the intervals during (T1–T2) and after (T2–T3, T3–T4, T4–T5) the intervention period (measured in the waiting-list group after the first 8 weeks and in the intervention group). This will allow us to compare the rate of change in those receiving no intervention (T0–T1) with those receiving the intervention (T1–T5) while accounting for the fact that data are nested in individuals and, therefore, correlated. Intervals will be entered as a categorical variable (five levels) using dummies. Model fit of models with random intercepts (at the participant level) and models with random intercepts and random slopes (at the interval level) will be compared using likelihood ratio tests.

Emotional instability and quality of the relationship will be included as covariates because they are expected to influence the difference between groups. Coach will be introduced into the analysis as a random factor to estimate the variability attributable to the coach. For goal attainment, descriptive statistics will be used to calculate the total number of goals set per domain. Mean goal attainment scaling scores (*T*-scores) will be calculated with a standard formula [38] for each measurement time point.

All analyses will be carried out according to the intention-to-treat principle using IBM SPSS statistics 22.0 for Macintosh. All tests of significance will report mean change and will be two-tailed, with α set at 0.05.

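### The planned follow-up analysis (changes per interval and a rate-of-change comparison) does not answer the aim of showing that effects are maintained at 3, 6 and 12 months

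*Protocol article*

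**What the plan says.** In the protocol article, Study aim and hypotheses, the third aim is to find out "whether these effects are maintained after 3, 6 and 12 months".

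Under Statistical analyses, Quantitative measures, the ANCOVA covers only the post-intervention outcome. The later visits are analysed in a linear mixed model that estimates a change in the waiting-list interval and "fixed effects for change in the intervals during (T1–T2) and after (T2–T3, T3–T4, T4–T5) the intervention period". On coding, the section says: "Intervals will be entered as a categorical variable (five levels) using dummies". The stated use of the model is to "compare the rate of change in those receiving no intervention (T0–T1) with those receiving the intervention (T1–T5"). On testing, it says: "All tests of significance will report mean change and will be two-tailed, with α set at 0.05".

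The section names no contrast of a 3-, 6- or 12-month level with the pre-programme level and none from end of programme to those visits. It gives no criterion for calling an effect maintained. Under Control group, waiting-list participants receive the programme after their post-test, so no untreated group exists from then on.

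**The concern.** Maintenance is a statement about level: is the gain still there at a given visit, and how much of it has gone? The model's named quantities are changes from one visit to the next, and a comparison of those changes with change on the waiting list. After the programme, a flat course can equal a flat waiting-list course whether the gain was large, small or absent. A slow decline is spread over three coefficients, none of which measures the total.

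With nothing else named, three non-significant follow-up changes are the pattern most easily read as maintenance. Small numbers and dropout make that pattern more likely, so an error of this kind would favour the programme. The claim at stake is twelve-month durability.

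**Working it through.** **The plan's own figure.** Sample size gives 80 caregivers from "within-between interaction with a mean effect size of 0.2", alpha 0.05, power 85% and 25% loss. It does not state the metric of 0.2, the number of measurements or the correlation. Reading 0.2 as Cohen's f, with two measurements and correlation 0.5 (both assumed), and N = 60:

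- Noncentrality = f² × N × m / (1 − ρ) = 0.04 × 60 × 2 / 0.5 = 9.6. With 1 and 58 degrees of freedom, power is 0.861; N = 58 gives 0.849.
- 60 / (1 − 0.25) = 80, so the figure is reproduced.
- On this reading the between-group difference in change is 4f = 0.8 SD. Reading 0.2 as Cohen's d (f = 0.1) would instead require 228 completers, or 304 enrolled.

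**Inputs for the illustration.**

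- Completers: 80 × 0.75 = 60.
- Size of the gain: 0.3 SD, the top of the range that Background cites for earlier e-health studies ("effect sizes ranging from 0.2 to 0.3").
- Assumed: SD 1 at each visit, equal within-person correlation r of 0.5 to 0.8, the whole gain lost between end of programme and 12 months in three equal steps, each interval tested two-sided against zero at 0.05, and intervals correctly aligned to the programme in both arms.

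**Formulas.**

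- Standard error of any within-person change: √(2(1 − r)/60), which is 0.129, 0.100 and 0.082 at r = 0.5, 0.7 and 0.8.
- Power of one interval test: Φ(0.1/SE − 1.96).
- Power of the contrast from end of programme to 12 months: Φ(0.3/SE − 1.96).
- Probability that all three interval tests miss: by simulation, because adjacent changes are correlated.

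| r | One interval test | All three miss | Single contrast |
|---|---|---|---|
| 0.5 | 12% | 66% | 62–64% |
| 0.7 | 17% | 53% | 84–85% |
| 0.8 | 23% | 40% | 95–96% |

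In the last column the lower value comes from paired tests in simulation and the higher from the normal formula.

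**Sensitivity.**

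- A 0.2 SD gain lost evenly: all three miss in about 77%, 72% and 65%.
- A 0.5 SD gain lost evenly: about 36%, 15% and 4%.
- A 0.3 SD gain lost within one interval: about 33%, 13% and 4%.
- A 0.8 SD gain lost evenly: about 2% at r = 0.5.

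**The comparison the article does state.** Suppose each follow-up change is instead compared with the waiting-list change. Take the latter as truly zero, estimated from 30 waiting-list completers, independent, and not rescaled for interval length. At r = 0.5 the standard error rises from 0.129 to √(1/60 + 1/30) = 0.224. The probability that no follow-up interval differs significantly, although a 0.3 SD gain is wholly lost, is about 85%, 82% and 79% at the three correlations. A normal approximation gives values one to two points lower. On this reading the loss is harder to see than in a test against zero.

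**The case against.** A reader might infer that the plan tests each interval change against zero and counts a non-significant result as maintained. The article says neither. The sentence on two-tailed testing is general, and the only comparison spelled out is with the waiting-list interval. The plan should not be charged with that rule; the point is only that the reading is left open.

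The T1–T5 comparison can also be read as one span from programme start to 12 months. On that reading it says something about the 12-month level. It still says nothing separate about 3 and 6 months, and it merges the gain with any later loss.

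Contrast lists are often left to an analysis plan, and the model's coefficients can be summed. That is true, and it is why the repair is cheap. But the article does more than stay silent: it commits to particular follow-up quantities and a purpose for them, and these do not answer its own aim. Contrasts chosen after the results are seen would be post hoc.

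The size of the problem depends on the assumptions. A reader might conclude that complete loss would most likely go unnoticed. That holds for a small gain lost gradually, not generally: it fails for a sudden loss, for high correlation, or under the 0.8 SD reading that reproduces the sample size.

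Finally, the primary hypothesis rests on the randomized ANCOVA at the first post-test and is untouched.

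**Conclusion.** The point holds in a limited form. The stated analysis of the follow-up period does not estimate what the maintenance aim asks for, whatever the effect size.

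The practical risk varies. For a 0.3 SD gain lost evenly, with 60 completers and correlation 0.5 to 0.8, three interval tests against zero miss the complete loss in about 66% to 40% of trials. One cumulative contrast on the same data detects it with about 62% to 95% power. Completers, correlation, pattern of loss and the test against zero are assumptions of the illustration, not statements of the article.

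The change should be made, but the main efficacy test does not depend on it.

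**What to change.** In the mixed-model paragraph of Quantitative measures, state that the third aim is answered from the same model by cumulative contrasts (sums of interval coefficients), each with a 95% confidence interval:

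- (a) from the participant's own pre-programme value to each of the 3-, 6- and 12-month visits, to show whether a gain is still present;
- (b) from end of programme to each of those visits, to show the size of loss not excluded.

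Report (a) as gain still present, not as fully maintained, and always alongside (b). A lower bound of (a) above zero is not enough alone. A 0.8 SD gain that has faded to 0.3 SD would meet it with probability Φ(0.3/SE − 1.96), about 64% at r = 0.5 and 96% at r = 0.8.

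State also that a non-significant interval change is not evidence of maintenance. Describe the results as within-person changes, because controls receive the programme after their post-test.

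The cost is a few sentences and linear contrasts of coefficients already estimated, with no new data or visits. The downside is that some outcomes will be reported as maintenance not shown. With 60 completers the half-width of (b) is 1.96 × SE, or 0.25 SD at r = 0.5 and 0.16 SD at r = 0.8, which is large beside a gain of 0.2 to 0.3 SD.

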#### Control group

Participants in the control group will be placed on a waiting list for 8 weeks. After they complete the post-test assessment, they will receive the online self-management intervention. They will receive the same pre-test and post-test attention from the research team as the experimental group.

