### Procedure

Participants will be assessed at five time points: (T_0_) baseline assessment, (T_1_) post-intervention or waiting-list assessment (8 weeks), (T_2_) post-intervention assessment for waiting-list (8 weeks after T_1_), (T_3_) 3-month follow-up, (T_4_) 6-month follow-up, and (T_5_) 12-month follow-up. Figure 2 shows the schedule of enrollment, procedures and mixed-method assessments per condition.

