#### Intervention costs

To provide a comprehensive presentation of the value of “Partner in Balance,” a cost-consequence analysis will be conducted. This is a listing of all the relevant costs and consequences (outcomes) of the intervention. Costs will be based on the Dutch guidelines for cost calculations in health care [53]. Formal and informal resources used by the caregiver and care recipient will be mapped by means of the Resource Utilization in Dementia – shortened version (RUD-lite) [54], which includes information on hospital costs, contacts with the GP or other health care professionals, home care, day care, admissions to a nursing home or home for the elderly, medication and acquisition of goods/aids. Costs are calculated by multiplying the volume of resource use by the cost price per resource unit and include the period from the baseline assessment up to the last follow-up measurement (12 months). Intervention costs include time spent on the intake and evaluation session, e-mail contact, the coach training sessions, materials, and coach supervision. The coaches will register the amount of time spent on the intake, evaluation session and e-mail contact on a structured registration form. All costs are expressed in Euros and are adopted from Hakkaart-van Roijen [53].

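### The total-period mixed model does not fit the visit definitions, and its comparison of change in T0–T1 with change in T1–T5 is neither a comparison of rates nor a randomised one

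*Protocol article*

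**What the plan says.** All references are to the protocol article.

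- **Procedure.** "Participants will be assessed at five time points", but six labels follow, T0 to T5. T1, at 8 weeks, ends treatment in the intervention arm and ends waiting in the control arm. T2, 8 weeks later, is the "post-intervention assessment for waiting-list"; no T2 is defined for the intervention arm.
- **Control group.** The waiting list crosses over at T1: "After they complete the post-test assessment, they will receive the online self-management intervention".
- **Quantitative measures, mixed model.** One fixed effect is for "the change during the waiting-list interval (T0–T1 as measured in the waiting-list group only". The programme interval is T1–T2 and the post-programme intervals are T2–T3, T3–T4 and T4–T5, with data from both arms. Interval enters as five categories coded with dummies. The model is then said to "compare the rate of change in those receiving no intervention (T0–T1) with those receiving the intervention (T1–T5".
- **Quantitative measures, ANCOVA.** The primary hypothesis is tested separately, by comparing the arms on the post-intervention outcome adjusted for its baseline value.
- **Study aim and hypotheses.** Aim 3 asks "whether these effects are maintained after 3, 6 and 12 months". Aim 4 speaks of the programme's impact on resource use, costs and health outcomes.
- **Intervention costs.** Costs "include the period from the baseline assessment up to the last follow-up measurement (12 months".

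**The concern.** The mixed model is the only analysis stated for aim 3 on the primary and secondary outcomes, and it is described in enough detail to be followed as written. Followed literally, it leaves the intervention arm's treated interval without a place. That interval is the only treated change that has a randomised comparator. The arm must also supply a T1–T2 change for which it has no T2 visit.

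The comparison built on the model is a second problem, independent of the labels. It sets a short untreated span against a much longer one that is mostly post-treatment follow-up, in a period when no one is untreated. Change with time, disease progression or regression to the mean could then be reported as a programme effect, or a lasting effect could be reported as fading.

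**Working it through.** **1. The labels side by side**

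| | Intervention arm | Waiting list |
|---|---|---|
| Procedure: treated in | T0–T1 | T1–T2 |
| Procedure: visits | T0, T1, T3, T4, T5 (five) | T0 to T5 (six) |
| Model: T0–T1 taken from | not used | used, untreated |
| Model: programme interval | T1–T2 | T1–T2 |

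Only the waiting-list column agrees with itself. The stated count of five visits fits the intervention arm only; the model's five intervals need six visits and fit the waiting list only.

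**2. Interval lengths**

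One month is 365.25/12/7 = 4.35 weeks, so 12 months is 52.2 weeks. T1 is week 8 and T2 is week 16. The text does not fix the follow-up origin consistently, so all three are shown.

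| Follow-up counted from | T3 (week) | T5 (week) | T1–T5 (weeks) | Multiple of 8 weeks |
|---|---|---|---|---|
| T0 | 13.0 | 52.2 | 44.2 | 5.5 |
| T1 | 21.0 | 60.2 | 52.2 | 6.5 |
| T2 | 29.0 | 68.2 | 60.2 | 7.5 |

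The costing section implies the first row. In that row T3 (week 13) comes before the waiting list's T2 (week 16), against the order in the Procedure section.

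**3. Dummies compared as raw change**

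With no treatment effect and a constant drift b per week, T0–T1 shows 8b and T1–T5 shows 44.2b, 52.2b or 60.2b. The spurious excess is 36.2b, 44.2b or 52.2b. The documents give no drift, so b is an assumption:

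- b = 0.005: excess 0.18, 0.22 or 0.26
- b = 0.01: excess 0.36, 0.44 or 0.52

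**4. Change divided by time**

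Constant drift now cancels, but another error appears. Take an effect of 1 unit, gained in the 8 treated weeks and fully kept. Its rate over treatment is 1/8 = 0.125 per week. Over T1–T5 it is 1/44.2 = 0.0226, 1/52.2 = 0.0192 or 1/60.2 = 0.0166 per week. Full maintenance therefore looks like loss.

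**5. Simulation check**

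Assumptions: 30 evaluable participants per arm, between- and within-person SD 0.7 each, 150 runs, visit dummies with a random intercept, no covariates or coach effect. Follow-up ran from the end of each arm's programme. The literal version needs an invented T2 in the intervention arm.

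| Scenario | Model | T0–T1 | T1–T2 | T1–T5 | ANCOVA at T1 |
|---|---|---|---|---|---|
| Effect 0.40, no drift | literal labels | 0.17 | 0.18 | 0.19 | 0.40 |
| Effect 0.40, no drift | re-aligned | 0.00 | 0.40 | 0.40 | 0.40 |
| No effect, drift 0.01/week | re-aligned | 0.10 | 0.07 | 0.58 | −0.02 |

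With literal labels, T1 pools treated and untreated people, so about half the effect (0.40/2 = 0.20) falls into the supposedly untreated interval. In the last row the T1–T5 change exceeds the T0–T1 change by 0.58 − 0.10 = 0.48, against 52.2 × 0.01 = 0.52 from step 3. Monte Carlo error for a simple waiting-list 8-week change is about 0.7 × √(2/30)/√150 = 0.015.

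**6. Sample size**

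The stated inputs are effect size 0.2 (read as Cohen's f), alpha 0.05, power 85% and 25% loss. The number of measurements m and the correlation ρ are not given. With m = 2 and ρ = 0.5 assumed, the noncentrality is N·f²·m/(1 − ρ) = 60 × 0.04 × 2/0.5 = 9.6. Power is 86.1% at N = 60 and 84.9% at N = 58, and 60/0.75 = 80, as planned. Among m = 2 to 6 and ρ = 0.3, 0.5, 0.6 and 0.7, results run from 27 to 110 and only this pair gives 80. The figure is thus consistent with a two-measurement design and needs no contribution from the total-period model.

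**The case against.** The strongest reply is that the model makes sense on a clock aligned to each arm's treatment start. The waiting list would then supply one waiting, one programme and three follow-up intervals, and the intervention arm the last four. That gives exactly five levels and explains why the untreated interval comes from the waiting list alone. This stands as the likely intent. A reader might infer that intervention-arm data will in fact be assigned to the wrong interval; the documents do not support that. They show an unstated rule that clashes with the visit labels.

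The model also estimates each interval separately, so an 8-week against 8-week comparison is available. In the drift scenario it is close to balanced (0.10 against 0.07). The mismatch lies in the T0–T1 versus T1–T5 sentence.

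The lack of a later comparator follows from an openly stated waiting-list design, and within-person follow-up can describe maintenance. That is fair for the design. It does not justify presenting the T1–T5 comparison as treated against untreated.

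Other stronger readings also go too far:

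- **A treated span of more than a year.** This holds only if follow-up starts at T2; the costing section implies about 44 weeks. Fig. 2, which shows the schedule per condition, was not available for this check and may settle the origin.
- **Cost windows of 60 and 68 weeks in the two arms.** This requires follow-up from the end of each arm's programme, which the text does not state. The cost-consequence analysis is a listing with no stated between-arm test.
- **A definite drift bias.** Any figure rests on an assumed drift and applies to raw change only.
- **A threat to the main result.** The primary hypothesis is tested by the between-arm ANCOVA, not by this model.

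**Conclusion.** The point holds in limited form. The mixed model and the visit definitions contradict each other on where the intervention arm is treated and whether it has a T2. The T0–T1 versus T1–T5 comparison is unsound on either time axis: the spans differ by a factor of about 5.5 to 7.5, dummies do not estimate rates, T2–T5 is follow-up and not treatment, and the contrast is non-randomised and confounded with time.

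The numerical consequences rest on the assumptions shown: a constant drift of 0.005 to 0.01 per week for raw change, and an effect reached within 8 weeks and fully kept for change per week. The contradiction and the lack of a comparator need no such assumption. What is affected is aim 3 and the way long-term costs under aim 4 may be worded. The ANCOVA at T1 and the sample size stand. Severity: should-fix.

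**What to change.** - State the time axis: visits dated from randomisation, or explicitly re-aligned to each arm's treatment start. State the origin of the 3-, 6- and 12-month visits and make it agree with the costing period.
- Reconcile the visit count in the Procedure section, by arm.
- Keep both arms' T0–T1 data in the model and take the treatment effect from the randomised T0–T1 contrast only.
- Delete the T0–T1 versus T1–T5 rate comparison.
- Report the waiting list's T1–T2 change separately, as a before-after replication.
- Report the 3-, 6- and 12-month results as within-person change with 95% CI, labelled uncontrolled.
- Present 12-month costs as descriptive, not as an effect of the intervention.

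The same data are used and no visit or participant is added. The work is rewording the model and aims 3 and 4. The price is a weaker long-term claim: maintenance is described, not shown against a control.

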**Methods/design:**

A mixed-method, single-blind, randomized controlled trial with 80 family caregivers of community-dwelling people with (very) mild dementia will be conducted. Participants will be randomly assigned to either the 8-week blended care self-management program “Partner in Balance” or a waiting-list control group. Data will be collected pre intervention and post intervention and at 3-, 6- and 12-month follow-ups. Semi-structured interviews will be conducted post intervention. A process evaluation will investigate the internal and external validity of the intervention. Primary outcomes will include self-efficacy and symptoms of depression. Secondary outcomes will include goal attainment, mastery, psychological complaints (feelings of anxiety and perceived stress), and quality of life. Possible modifying variables such as caregiver characteristics (quality of the relationship, neurotic personality) and interventional aspects (coach) on the intervention effect will also be evaluated. A cost-consequence analysis will describe the costs and health outcomes.

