#### Additional measures

Quality of the relationship is rated with four items of the *University of Southern California Longitudinal Study of Three-Generation Families measures of positive affect* [49]. The items indicate (1) general closeness, (2) communication, (3) similarity of views about life, and (4) degree of getting along. Scores range from 1 (not at all) to 4 (very). The value system for the 1024 states uses a best–worst scaling valuation method, providing a single summary score, anchored at 0 (“no capability”) and 1 (“full capability”). Good reliability was found in a previous study [50].

The *NEO Five-Factor Inventory (NEO-FFI)* [51] measures personality. The 12-item Neuroticism domain will be used to identify individuals who are prone to psychological distress. This domain assesses six traits: anxiety, angry hostility, depression, self-consciousness, impulsiveness and vulnerability [52]. The reliability of the Dutch version of the NEO-FFI is good [51].

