### Statistical analyses

#### Quantitative measures

Prior to the analysis, data will be checked for missing values, outliers, and normality. Possible differences between the study groups’ baseline characteristics will be tested with *t* tests for continuous variables and χ^2^ tests for categorical variables. In case of missing data, we intend to test if data is missing completely at random (MCAR) based on a comparison of the baseline characteristics of study completers and participants with missing values. If *p* <0.05 for (one of) the variables in the model, the missing values are non-random. In case of data MCAR, the specification of a missing value or dropout model is not necessary and list-wise deletion will be applied. In case of missing data not at random, we will apply a multiple imputation-based strategy [56].

To examine differences in the outcomes of the intervention and the waiting-list control groups during the intervention period, an analysis of covariance (ANCOVA) will be conducted with post-intervention outcome as the dependent variable, intervention (“Partner in Balance,” waiting-list control group) as the between-subjects variable and the pre-intervention outcome, emotional instability, quality of the relationship, educational level and relationship to the care recipient as covariates. Each outcome will be assessed as a dependent variable. Group differences in the post-intervention outcome adjusted for its baseline value will be examined to test the primary hypothesis. If differences are found, the inter-group effect size will be calculated according to Cohen’s *d*.

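### Neuroticism and relationship quality are named as possible effect modifiers but enter the models only as covariates, so the analysis as written estimates no modification; relationship quality also carries the ICECAP-O scoring rule

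*Protocol article*

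**What the plan says.** Three parts of the protocol article bear on this point.

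- **Abstract, Methods/design.** The article undertakes to evaluate "Possible modifying variables such as caregiver characteristics (quality of the relationship, neurotic personality) and interventional aspects (coach) on the intervention effect".
- **Statistical analyses, Quantitative measures.** The ANCOVA that tests the primary hypothesis takes the pre-intervention outcome together with "emotional instability, quality of the relationship, educational level and relationship to the care recipient as covariates". After the linear mixed model is described, the reason for two of these variables is given: "Emotional instability and quality of the relationship will be included as covariates because they are expected to influence the difference between groups". Coach is handled differently: "Coach will be introduced into the analysis as a random factor to estimate the variability attributable to the coach". Neither model is given a product term between arm (or interval) and neuroticism or relationship quality, and no subgroup contrast is described.
- **Questionnaires, Additional measures.** On neuroticism: "The 12-item Neuroticism domain will be used to identify individuals who are prone to psychological distress". On the relationship scale: "Quality of the relationship is rated with four items of the" named family-study measure, each item scored 1 to 4. The same paragraph then continues: "The value system for the 1024 states uses a best–worst scaling valuation method, providing a single summary score", with anchors of 0 and 1 for capability. Under Secondary outcomes, the same number of states, valuation method and anchors are given for the ICECAP-O, which has five attributes.

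**The concern.** A variable that changes the difference between groups is an effect modifier. Estimating that change needs a term that lets the group difference vary with the variable. A covariate entered on its own adjusts the outcome level and usually improves precision, but it holds the group difference fixed. The reason given for the two covariates therefore describes one analysis and the model describes another.

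At stake is the modifier question raised in the abstract. Without a written term it has no estimate. If terms are chosen after the data are seen, the choice of modifier, outcome and time point is open to selection.

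The scoring sentence raises a smaller, separate matter. Relationship quality is both a declared modifier and a covariate in the primary ANCOVA, and the only rule given for turning its items into one score belongs to another instrument.

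**Working it through.** **1. What the written model can estimate.** Let A be arm (0/1), M a modifier, Y0 and Y1 the outcome before and after the intervention.

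- As written: E(Y1) = b0 + b1·Y0 + b2·A + b3·M + other covariates. The group difference is b2 at every value of M. The coefficient b3 is the association of M with the outcome, not modification.
- With a product term b4·A·M added, the group difference is b2 + b4·M, and b4 is the modification.

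The mixed model has the same gap: its interval effects are not allowed to vary with M.

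**2. What the planned sample size was for.** The Sample size section gives effect size 0.2 for a repeated-measures within-between interaction, alpha 0.05, power 85%, 25% loss and 80 participants. Read 0.2 as Cohen's f and assume two measurements (m) and correlation 0.5 (rho), neither of which is stated:

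- noncentrality = f²·N·m/(1 − rho) = 0.04 × 60 × 2 / 0.5 = 9.6, on 1 and 58 degrees of freedom; power 0.861 with N = 60
- 60 / 0.75 = 80

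The stated 80 is reproduced. It powers group by time, not group by modifier.

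**3. Precision of a group-by-modifier term.** Inputs: 60 completers (80 × 0.75); equal arms; M standardised and unrelated to arm, as expected of a baseline measure; baseline-outcome correlation r of 0.5 to 0.7, an assumption because the article gives none.

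SE(b4) = √(1 − r²) × 2 / √N, in outcome SD per SD of the modifier. The effect detectable with 85% power (two-sided 0.05) is (1.96 + 1.036) × SE.

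| r | SE, N = 60 | 95% CI half-width (1.96 × SE) | Effect at 85% power |
|---|---|---|---|
| 0.5 | √0.75 × 2/√60 = 0.224 | 0.44 | 0.67 |
| 0.6 | √0.64 × 2/√60 = 0.207 | 0.41 | 0.62 |
| 0.7 | √0.51 × 2/√60 = 0.184 | 0.36 | 0.55 |

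With all 80 analysed, the 85% figures are 0.58 (r = 0.5) to 0.48 (r = 0.7). With 60, power for an interaction of 0.2 SD per SD is about 14% to 19%, and for 0.4 about 43% to 58%. A simulation at r = 0.5 and N = 60 gave 13% and 39%, close to the formula.

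An interaction of 0.55 to 0.67 means that the group difference shifts by 2 × 0.55 = 1.1 to 2 × 0.67 = 1.34 outcome SD between caregivers one SD below and one SD above the modifier mean. Only very large modification would be detected reliably.

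**4. Scoring of relationship quality.** Four items at four levels give 4⁴ = 256 profiles. The stated 1024 equals 4⁵, which fits five four-level attributes and so matches the five attributes of the ICECAP-O. A simple sum of the four items would run from 4 × 1 = 4 to 4 × 4 = 16, but the article does not say whether the items are summed, averaged or combined in some other way.

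**The case against.** The best case for leaving the text alone has four parts.

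- Modification is not one of the four numbered aims under Study aim and hypotheses (validity, superiority, maintenance of effects, cost-consequence). It appears as a possibility in one abstract sentence, and exploratory interaction terms are often left to an analysis plan, which is not shown here.
- The stated reason could be loose wording for prognostic adjustment, since the ANCOVA lists both variables beside education and relationship to the care recipient without any language of modification.
- The added terms would be imprecise.
- The 1024-state sentence is an evident carry-over that an analyst would not try to apply to four items.

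Much of this stands, and it limits the point. It does not remove it. The article does more than omit a detail: it names a handling and gives a reason that this handling cannot serve, and the abstract makes the modification reading the natural one. If prognostic adjustment was meant, the sentence still needs rewording and the abstract's promise still has no analysis. Low precision is a reason to label the terms exploratory.

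A reader might infer three stronger things that the article does not support:

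- **That the modifier question cannot be answered.** Both variables are measured, no sentence rules out interactions, and an unseen plan may contain them.
- **That a significant covariate coefficient will be reported as moderation.** Nothing says covariate coefficients will be interpreted in that way.
- **That the primary comparison is compromised.** A covariate-adjusted comparison of randomised groups is valid without interaction terms.

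**Conclusion.** The point holds as a conflict between the stated reason and the stated model. As written, the analysis gives no estimate of modification by neuroticism or relationship quality. The primary between-group ANCOVA is unaffected. The scoring sentence for relationship quality is wrong as it stands, with a small consequence: the coding of one primary-model covariate is left undefined.

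The change is worth making but does not block the trial. Any modification estimate will be imprecise, with 85% power only at about 0.67 to 0.55 SD per SD of the modifier. That range rests on 60 completers, equal arms, and the assumed correlation of 0.5 to 0.7. The conclusion also takes emotional instability to be the NEO-FFI Neuroticism score, the only matching measure described. The finding that the written model has no modification parameter depends on none of the numerical assumptions.

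**What to change.** 1. Keep the main-effect ANCOVA as the primary analysis.
2. For the primary outcomes at T1 (both CSES totals and the CES-D), add arm × neuroticism and arm × relationship quality, one at a time, with the modifier continuous and centred. Report each with its 95% confidence interval and label it exploratory. T1 is the right place because the waiting-list group receives the programme afterwards.
3. Reword the rationale after the mixed model: the two characteristics are included as expected predictors of outcome, and modification is examined by the interaction terms.
4. Delete the 1024-state and capability sentence from the relationship-quality description and state the scoring actually intended, for example a sum of 4 to 16 if the sponsor confirms it.

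The cost is 3 outcomes × 2 modifiers = 6 exploratory estimates and two corrected passages of text, with no new data. At the 5% level, six such tests would give 6 × 0.05 = 0.3 false positives on average if no modification exists, which is a further reason to report intervals and not verdicts. The Trial status section says recruitment is still under way, so the terms can be fixed before analysis.
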